# Efficacy of Cognition Support Formula® on cognitive function in older adults with subjective cognitive impairment: a protocol for a 26-week, randomised, double-blind, placebo-controlled trial

**DOI:** 10.1186/s13063-019-3431-3

**Published:** 2019-06-10

**Keywords:** Subjective cognitive impairment (SCI), Herbal medicine, Cognition Support Formula®, CogState®, EEG, Randomised controlled trial

## Abstract

**Background:**

Due to an ageing population in Australia there has been an increase in the number of older adults with subjective cognitive impairment (SCI), a self-reported decline in cognitive function associated with an increased risk of mild cognitive impairment and dementia. There is no current, recommended treatment for SCI; therefore, the effectiveness of a supplement approved by the Therapeutic Goods Association that has the potential to enhance cognitive function in an at-risk cohort should be tested. The primary aim of this proposed research is to determine the efficacy of 6 months of treatment with BioCeuticals Cognition Support Formula® (containing *Bacopa monniera* (brahmi), *Ginkgo biloba, Panax ginseng* and alpha-lipoic acid) on cognition in older adults with SCI (utilising the CogState® one card learning and identification tests as co-primary outcome measures of visual short-term memory and attention; mean speed (ms), accuracy (%), and total number of hits, misses, and anticipations) compared with placebo. The secondary aims are to assess an improvement in other cognitive domains (executive functioning, processing speed, and working memory), evaluate safety, adverse effects, and determine efficacy on mood, fatigue, and neurocognition. It is expected that improvements across the study timepoints in the co-primary outcomes in the active treatment group (compared with placebo) will be evident.

**Method:**

One-hundred and twenty participants will be recruited for the randomised, double-blind, placebo-controlled study. Participants will be randomly assigned to one of the treatment groups (active or placebo) at a 1:1 ratio, and will be required to complete a series of cognitive (using CogState®), mood (using the Depression, Anxiety, Stress Scale (DASS-42) and Short Health Anxiety Inventory (SHAI)), and fatigue (using the Functional Assessment of Chronic Illness Therapy Fatigue Scale (FACIT-F)) tasks at baseline (0 months), the midpoint (3 months), and the endpoint (6 months). These tasks will be evaluated between timepoints (baseline vs. midpoint, midpoint vs. endpoint, and baseline vs. endpoint). Neurocognition will be measured by electroencephalography at baseline and at the endpoint in half of the participants. Adverse effects will be documented over the 6-month trial period.

**Discussion:**

This is the first study to test the efficacy of Cognition Support Formula® on cognition in older adults with SCI. As people with SCI have an increased risk of dementia, and there are limited treatments options for this population, it is important to assess a supplement that has the potential to enhance cognitive function.

**Trial registration:**

Universal Trial Number (UTN), U1111–1196-9548. Australian New Zealand Clinical Trials Registry, ACTRN12617000945325. Registered on 30 June 2017.

**Electronic supplementary material:**

The online version of this article (10.1186/s13063-019-3431-3) contains supplementary material, which is available to authorized users.

## Background

### Subjective cognitive impairment

Subjective cognitive impairment (SCI) is a concern an individual has about a decline in their cognitive functioning, particularly within the memory domain [1–3]. Although most subjective reports of cognitive decline are about memory, SCI can also relate to perceived changes in attention, executive functioning, and language. Furthermore, SCI is correlated with high scores of depression and anxiety and low future cognitive performance [4]. In contrast to normal ageing, SCI is evidenced by a future objective decline in cognition over a shorter period of time than what is expected for age-related cognitive decline [5]. Hence, SCI is related to a significant future decline in cognition, rather than aged-related deficits in current memory [6].

SCI has been found to be associated with an increased risk of mild cognitive impairment (MCI) and Alzheimer’s disease (AD), the most common form of sporadic late-onset dementia [2, 7, 8]. A longitudinal study of older adults found that 54% of older adults with SCI show a cognitive decline over a 7-year follow-up period compared with only 15% with no SCI [9]. Approximately 79% of those people with SCI developed MCI, and 21% developed AD over 7 years [9], representing a significantly increased risk of future decline for this population. It is important not to ignore reports of cognitive impairment by older adults, as the literature suggests these could be early signs for the future development of AD and MCI [10].

Due to an ageing population in Australia, cognitive impairment is becoming more prevalent. The estimated global prevalence of SCI ranges between 25 and 50% in older adults [11]. In terms of prevalence between sexes, older females more often report SCI than older males [12]. This was evidenced in a study of older adults 64 years of age and above, where 35.2% of females compared with 28% of males in the study reported SCI [12]. In addition, older adults with higher levels of education compared with older adults with lower levels of education are more likely to report cognitive impairment as they are thought to have more insight into the changes in their own cognitive functioning [12].

Older adults reporting SCI are more likely to have heightened levels of anxiety and depression, which can further impact on cognitive performance and increase dementia risk, and vice versa [6, 13]. Furthermore, evidence of heightened fatigue and low energy levels have been found to be associated with poor cognitive performance in older adults with SCI [5].

### Current treatments for SCI

Current treatments for older adults with SCI are limited, with most published clinical trials utilising nutraceuticals including soybean-derived phosphatidylserine (SB-PS) and multivitamins containing extracts of *Bacopa monniera* (whole plant) and *Ginkgo biloba* leaf extract [14, 15]. These studies have documented small effects in terms of improvements in cognitive tasks (working memory, recognition memory, and recall) where short trial periods were utilised (12 weeks [14] and 16 weeks [15]). Unfortunately, there is no evidence to determine whether these effects were stable over the trial period (possibly a significant increase, then a tapering off), or whether the cognitive improvements occurred shortly after treatment, or towards the end of the trial period. A longer trial period of 6 months that includes midpoint testing is required to clarify the stability and longevity of any changes. This would prove most fruitful in determining whether such a treatment could manage SCI in the long term.

### Cognition Support Formula®

Cognition Support Formula® (BioCeuticals Pty Ltd) is a herbal and nutritional supplement commercially available over the counter in select pharmacies and via practitioners (e.g. naturopaths). Cognition Support Formula® incorporates extracts of four different ingredients into one formula—*B. monniera* (brahmi), *G. biloba*, *Panax ginseng*, and alpha-lipoic acid (ALA)—and is designed to enhance cognitive functioning and energy levels in older adults. Each of these active components will be reviewed briefly below, with evidence of their efficacy in improving cognition in older adults highlighted.

### *Bacopa monniera* (brahmi)

*B. monniera* (brahmi) is an aquatic plant utilised in the traditional Ayurvedic medical system in India to enhance memory and intellectual functioning and to promote longevity [16]. The active components of brahmi are identified as bacosides A and B [17]. Brahmi may be neuroprotective and memory enhancing, and have antioxidant effects [18]. The active bacosides are thought to increase cerebral blood flow and neurotransmitter modulation (acetylcholine, 5-hydroxytryptamine, and dopamine) [18]. Brahmi has been found to significantly improve memory acquisition and retention in immediate and delayed recall task in 36 older adults ingesting one 300 mg tablet/day for 12 weeks (compared with *n* = 45 in the control group) [16].

### *Ginkgo biloba* (ginkgo)

*G. biloba* (ginkgo) is a natural extract derived from the leaf of the Chinese ginkgo tree. Its bioactive constituents (flavonoids and terpenoids) are thought to have strong antioxidant properties, which assist in slowing down the progression of age-related diseases [19]. These components have been found to increase the blood supply by dilating blood vessels and reducing blood viscosity. The standardised extracts of ginkgo leaf (EGb 761) have been shown to increase positive mood, energy, and cognition [1, 19]. One study of 241 older adults showed an increase in scores on the Benton Visual Retention Test-Revised in two active groups (low-dose group, 1.9 ml undiluted ginkgo extract three times daily with a placebo; high-dose group, 1.9 ml of undiluted extract three times daily) for 24 weeks compared with a placebo [1].

### *Panax ginseng*

*P. ginseng*, or Korean ginseng, is an extract from the Araliaceae family of plants [20]. The active component is ginsenosides from three different groups: protopanaxadiol, protopanaxatriol, and oleanolic acid. The mechanism of action of ginseng is thought to be within the central nervous system with the modulation of neurotransmitter systems involved in the mediation of memory and cognition, including GABA, glutamate, dopamine, and serotonin [21]. Additionally, ginseng has been found to upregulate key neurotrophins involved in neuroplasticity including brain-derived neurotropic factor (BDNF) [22]. For a detailed review on the molecular mechanisms of ginseng compounds see Lü et al. [23].

In combination with ginkgo, ginseng has been shown to improve aspects of working memory and improved attention in younger adults [20]. Additionally, Sünram-Lea and colleagues found improvements in 15 participants regarding their processing speed and in episodic memory with an acute ingestion of 400 mg ginseng compared with a placebo group of the same sample size [24]. This outcome is of particular interest since episodic memory is a key deficit in adults with AD.

### Alpha-lipoic acid

ALA, a naturally occurring fatty acid, is a cofactor of some mitochondrial enzymes. ALA is a powerful nutrient that is able to recycle redox-active antioxidant vitamins such as E and C [25]. Mechanisms of action include an influence on neuronal energy production (reactivation of enzymes involved in glucose metabolism and glucose transport, i.e. a blood glucose lowering effect) and anti-oxidative and anti-inflammatory properties (downregulation of chronic inflammatory processes) [26].

In the literature, ALA has been found to stabilise cognitive functioning in older adults with AD [27]. Nine participants with probable AD took part in a non-randomised open-label study for an average of 337 days where they ingested 600 mg ALA daily [27]. Mini-Mental State Examination (MMSE) and the Alzheimer’s Disease Assessment Scale-cognitive (ADAS-cog) subscale scores were stable (i.e. no decline) for the trial duration.

### Adverse effects

The proposed study detailed in this protocol is a clinical trial which will document the safety and any adverse effects of Cognition Support Formula® which uses a combination of the four ingredients. Separately, however, minor adverse effects have been reported for brahmi, ginseng, and ALA. Morgan and Stevens [16] noted minor gastrointestinal upset in participants receiving brahmi treatment compared with placebo. Similarly, over a 4-week treatment period ingesting 1000 mg ginseng per day, mild gastrointestinal upset and insomnia were evidenced compared with placebo [28]. Gastrointestinal upset has been recorded as an adverse effect after ingesting ginkgo; however, this effect was not statistically significant compared with ingestion of placebo [1, 19].

Drug interactions have been reported for cyclophosphamide and levothyroxine, and these should be avoided when taking ALA due to their possible adverse effects. ALA can combine with these medications, which may lower blood sugar levels and thyroid hormone levels [29].

### Rationale and aims

Currently, there are limited treatment options for an older population reporting SCI. Due to this limitation, and the increased risk of developing MCI and dementia, the efficacy of any intervention claiming potential cognitive enhancement should be tested. As Cognition Support Formula® is a commercially available and listed medicine approved by the Therapeutic Goods Association (TGA) and it has the potential to improve cognition, its efficacy and safety in a cohort of older adults with SCI requires testing.

The primary aim is to determine the efficacy of 6 months of treatment with Cognition Support Formula® to improve cognition in older adults with SCI as measured by the one card learning test and the identification test (from the CogState® Pre-clinical Alzheimer’s Battery). These tests measure visual short-term memory and attention and will be considered as co-primary outcome measures as they are the most common areas of cognitive decline cited in the current literature for this population, and from the observations made in our laboratory [1–3]. The secondary aims are: 1) to assess an improvement in the cognitive domains of processing speed and working memory by utilising the detection test and the one back task (derived from the CogState® Pre-clinical Alzheimer’s Battery) and, in addition, executive functioning will be measured by the Groton Maze learning test (an additional CogState® test); 2) to assess the safety and adverse effects of Cognition Support Formula® compared with placebo; 3) to assess the efficacy of 6 months of treatment with Cognition Support Formula® compared with placebo on mood, as measured by the Depression, Anxiety, Stress Scale (DASS-42) and the Short Health Anxiety Inventory (SHAI), and fatigue and energy levels, as measured by the Functional Assessment of Chronic Illness Therapy Fatigue Scale (FACIT-F); and 4) to assess the efficacy of 6 months of treatment with Cognition Support Formula® on neurocognition compared with placebo by utilising psychophysiological measures (electroencephalography (EEG)) at baseline and at the endpoint.

In line with previous research examining individual constituents [1, 14, 16–25], we hypothesise that a 6-month dose of Cognition Support Formula® will improve cognitive functioning with minimal adverse effects in older adults with SCI compared with placebo. Due to limited literature in this area, exploratory analyses will be conducted in the domains of mood, fatigue, and neurocognition.

## Methods

### Trial design and setting

A randomised, double-blind, placebo-controlled 6-month trial will test the efficacy and safety of Cognition Support Formula® on cognition, mood, fatigue, and electrophysiology in older adults with SCI. The current study protocol (version 6) was designed in accordance with the SPIRIT guidelines [30] (see Additional file 1) and Good Clinical Practice guidelines (1996). Any changes to the study protocol will be communicated with the study investigative team, the Australian New Zealand Clinical Trials Registry (ANZCTR), and the Western Sydney University Human Research Ethics Committee. The study is being conducted in the NICM Clinical Laboratory and HEADBOX Laboratory at Western Sydney University, Campbelltown campus.

### Intervention

#### Active

Cognition Support Formula® contains clinically trialled ingredients to assist learning and memory. The composition of the formula components can be found in Table 1. The daily dose will be one tablet, twice daily (morning and night), for 6 months. Cognition Support Formula® is a dietary supplement made by BioCeuticals Pty Ltd, and is approved as a listed medicine by the TGA.

**Table 1 Tab1:** Composition of Cognition Support Formula® components

*Bacopa monniera* (bacopa) whole plant (equivalent to bacosides A)	4.00 g 90.00 mg
*Ginkgo biloba* (ginkgo) leaf (equivalent to ginkgo flavonglycosides) (equivalent to ginkgolides and bilobalide)	3.00 g 16.02 mg 4.02 mg
*Panax ginseng* (Korean ginseng) root (equivalent to ginsenosides Rg1, Re, Rf, Rg2, Rb1, Rb2, Rc, Rd)	212.00 mg 4.25 mg
R, S-alpha-lipoic acid	300.00 mg

#### Placebo

The placebo tablet contains an inert substance, which is matched for colour, smell, and taste to that of Cognition Support Formula®. The dose will be one tablet, twice daily (morning and night), for 6 months. The composition of components contained within the placebo tablet can be found in Table 2.

**Table 2 Tab2:** Composition of placebo components

Calcium hydrogen phosphate	782.00 mg
Microcrystalline cellulose	532.00 mg
Silica—colloidal anhydrous	12.00 mg
Magnesium stearate	12.00 mg

### Inclusion and exclusion criteria

The inclusion criteria for the proposed study are:≥ 60 years of ageEvidence of SCI as measured by:◦ Answering ‘yes’ to any of the following questions:▪ Do you feel your memory and thinking is getting worse?▪ Do you feel your memory and thinking has become worse over the past 2–3 years?▪ Are you concerned about your decline in memory and thinking?◦ No self-reported diagnosis of dementia or MCI◦ Scoring ≥ 23 on the Montreal Cognitive Assessment (MoCA) (as there is no standardised measure for SCI, a score of ≥ 23 will be utilised as a cut-off for SCI in line with previous literature [31, 32]Normal vision or vision corrected to normalNormal hearing or aided hearing

The exclusion criteria for the proposed study are:Severe depression, as measured by scoring > 19 on the 30-item Geriatric Depression Scale (GDS)Use of psychoactive medications or excessive alcohol intake (a maximum of 14 standard drinks per week) as recommended by the Australian Department of HealthNo caffeine 2 h prior to testingNon-smokersNo history of seizures or head injury (with loss of consciousness)Allergy to the study drug ingredients (ginseng, ginkgo, brahmi, or ALA)Participants previously taking ginseng, ginkgo, brahmi, or ALA (either separately or as a component of a supplement) are excluded from participation unless they have discontinued using these ingredients 8 weeks prior to testingLeft-handedness (only for EEG testing [33])Individuals with type 2 diabetes with a high fasting glucose level at baseline (> 8 mmol/L, according to Diabetes Australia) or those experiencing complications associated with their diabetic conditionDiagnosed psychiatric disorders including bipolar disorder, schizophrenia, personality disorders, drug and alcohol dependence, or substance abuse disordersPresence or history of severe renal and hepatic disordersHigh dependence on medical care (including medications) due to past or current medical conditions, for example cancerParticipants using cyclophosphamide and levothyroxine

### Recruitment and consent

Recruitment will be conducted by several methods, including advertisements in local newspapers, flyers at local community and residential aged-care facilities, internet sites (Western Sydney University and NICM websites), NICM and HEADBOX Lab newsletters, and social media promotion through Facebook and Twitter. In addition, participants will be referred from other trials conducted at HEADBOX Lab including a randomised, double-blind, placebo-controlled 12-week trial of Sailuotong (SLT) for mild cognitive impairment (Western Sydney University Human Research Ethics Committee Approval: H11878). Retention will be facilitated by regular contact during the clinical trial for screening, appointment reminders, and the three testing sessions (baseline, midpoint, and endpoint). Participants will provide informed verbal consent via telephone and written informed consent at the time of face-to-face screening to a member of the research team.

### Ethical guidelines

This research will be conducted in accordance with the International Ethical Guidelines for Biomedical Research Involving Human Subjects prepared by the Council for International Organisations of Medical Sciences (CIOMS) in collaboration with the World Health Organization (WHO), and the National Health and Medical Research Council (NHMRC).

### Privacy and data management

In accordance with ethical guidelines, the anonymity, confidentiality, and privacy of participants will be protected. All electronic data will be password protected. Hardcopy source data records will be kept in a locked cabinet in the office of the principal investigator during data collection and at completion of the study for an indefinite period of time. All publication material will refer to general trial results as aggregate data and no individual participant names or identifying information will be released. Participants are welcome to view their personal data at any time during the trial.

As this is an investigator-led study with a small sample size, a data management committee and auditing process is not required. Quality control, decisions pertaining to amendments of the protocol, coordination of the trial, and development of the secure database and trial forms will be completed by the research team. Data will be stored within the secure REDCap system (version 8.5.7) and coded utilising IBM SPSS statistics software (version 23).

### Sample size for co-primary and secondary outcome measures

This is the first study to utilise Cognition Support Formula® as a treatment for SCI, and thus there are limited comparable studies on which to base a sample size estimation. The most comparable study is by Lim et al. [34], who utilised a similar population (healthy older adults vs. people with MCI vs. AD) and a comparable measure to the current study as outlined in this protocol (CogState® battery). In order to see an improvement in performance in one test of the CogState battery® (group × time interaction) an effect size of Cohen’s *d* = .40 (i.e. Cohen’s *f* = .20, as *d* = 2*f*) at α = .05 was utilised [34].

To detect this effect size of Cohen’s *f* = .20 at α = .05 and 95% power, 100 participants across two groups are required. In order to account for a typical 20% drop-out, a total of 120 participants will need to be recruited (60 participants in the treatment group, and 60 in the placebo group). If the participation rate drops below the estimated number at any point during the course of the study, attempts to recruit additional participants will be made. Sample size may be re-estimated mid-course into the study to ensure adequate power. In this case, data will be unblinded by an objective third party to evaluate the treatment-effect size and power to assist with any potential sample size re-estimation.

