### Cognitive functioning evaluation

Participants will complete a number of computerised and pen and paper cognitive tests during the trial. Table 3 lists the cognitive, mood, and fatigue measures that will be utilised in this study. Further detail of these measures are given below.

The CogState® pre-clinical Alzheimer’s Battery of tests will be utilised to measure baseline, 3-month and 6-month changes in cognition. In addition to the battery, the Groton Maze learning test (CogState® test) will be completed by participants. CogState® is a computerised cognitive test battery that has excellent test-retest reliability ranging from .76–.93 (intra-class correlation coefficient) [34]. Participants will complete a practice trial prior to the main trial, in accordance with previous literature [34, 37]. There are no known practice effects associated with completing the practice. Practice trials will help to provide a ‘true baseline’ measure as errors are generally made during the first instance of completing the task. Participants will become familiar with the tasks during the practice trials, and this will therefore ensure equity in the measurement of task outcomes between the testing timepoints. The CogState® battery will be administered at baseline (0 months), the midpoint (3 months), and the endpoint (6 months), again with no known practice effects between time intervals. Furthermore, this cognitive testing method enables investigation into multiple areas of cognition including processing speed, attention, short-term memory, working memory, and executive function. The co-primary outcomes (one card learning and identification tests) measure visual short-term memory and attention, while the secondary outcomes (Groton Maze learning test, detection, and one back tests) measure executive functioning, processing speed, and working memory, respectively.

The DASS is a 42-item self-report instrument designed to measure the three related negative emotional states of depression, anxiety, and stress. Participants who consistently score higher than the normal range for depression (0–9), anxiety (0–7), or stress (0–14) (during baseline and midpoint sessions) will be advised to speak to their general practitioner. There is an expectation that participants will score higher in each of the three domains compared with a population without SCI [4].

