### Statistical analyses and dissemination

For each participant in each group and at each timepoint the following data from the primary and secondary outcome measures will be assessed. For the CogState® detection, identification, one card learning, and one back tests, we will assess mean speed (ms), accuracy (%), and total number of hits, misses, and anticipations; for the Groton Maze test, we will assess the total number of errors; and for the mood (DASS-42, SHAI) and fatigue (FACIT-F) outcomes, we will assess subscale and composite scores. CogState® data that are not normally distributed will be transformed using logarithmic base 10 transformations. Generalised linear mixed models with a between-subject factor of group (treatment, placebo) and within-subject factor of time (baseline, midpoint, endpoint) will be conducted to assess differences in continuous co-primary and secondary outcome measures. Planned simple contrasts will be conducted to assess all timepoints (baseline vs. midpoint, midpoint vs. endpoint, and baseline vs. endpoint). To handle any missing data, analysis of last observation carried forward will be undertaken within the intention-to-treat analysis model. The premise of the intention-to-treat model includes all participants in the final analysis even if non-compliance, withdrawal, or deviation from the protocol occurs [38]. Due to the nature of drop-outs in clinical trials, this analysis will be carried out on all five primary and secondary outcome measures of cognition and secondary outcomes of mood (DASS and SHAI) and fatigue (FACIT-F).

All tests will be two-tailed, α = .05. MANOVAs and Pearson’s correlations may also be utilised for assessment of psychophysiological data depending on the outcome measures assessed. All data will be analysed using SPSS. Results from the trial will be presented publicly to the community through peer-reviewed journals and scientific conference presentations. Additionally, individual trial outcomes will be forwarded to participants, with their consent.

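### The claim that 100 participants give 95% power for d = .40 cannot be reproduced from the stated inputs, and holds only under a within-person correlation that the sample-size section does not give

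*Protocol article*

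**What the plan says.** All of this is in the protocol article.

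- **Sample size for co-primary and secondary outcome measures.** The target effect is tied to an interaction: "group × time interaction) an effect size of Cohen’s *d* = .40". It is then converted: "i.e. Cohen’s *f* = .20, as *d* = 2*f*) at α = .05 was utilised". The result is "20 at α = .05 and 95% power, 100 participants across two groups are required", where the leading digits complete f = .20.
- **Statistical analyses and dissemination.** The model has group as a between-subject factor and three timepoints as the within-subject factor, with contrasts between each pair of timepoints. None is singled out as primary. On the error rate: "All tests will be two-tailed, α = .05".
- **Cognitive functioning evaluation.** The CogState battery is credited with "excellent test-retest reliability ranging from .76–.93 (intra-class correlation coefficient". The interval is not given, and the figure is not presented as an input to the sample size.

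**The concern.** The relation d = 2f belongs to a comparison of two independent means. Here it is used to obtain an f for a group × time interaction, where the link between a difference in SD units and f is different. The resulting pair of figures, 100 participants and 95% power, is also far more favourable than a simple two-group calculation for d = .40.

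What is at stake is how the result is read. With 95% power on record, a null finding would count as strong evidence against a 0.40 SD benefit. If the real figure is nearer one half, it would not. The same section allows the sample size to be re-estimated mid-course to secure adequate power, and that exercise also needs a sound planning effect.

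**Working it through.** **Inputs.** d = .40, f = .20, 95% power, 100 participants (50 per arm at 1:1) and the interaction label come from the sample-size section. Two-sided α = .05 and the three timepoints come from the statistical analysis section. The within-person correlation ρ is not given for this calculation, so it is varied below as an assumption.

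**Step 1. Trying to reproduce 100 with an interaction F test.** With m visits and sphericity, λ = N·m·f²/(1 − ρ), on (m − 1) and (N − 2)(m − 1) degrees of freedom. N needed for 95% power at f = .20:

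| ρ | 2 visits | 3 visits |
|---|---|---|
| .25 | 124 | **100** |
| .40 | **100** | 80 |
| .50 | 84 | 66 |
| .76 | 42 | 34 |
| .93 | 14 | 12 |

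So 100 appears at ρ of about .25 with three visits, or about .40 with two. Relaxing sphericity can come close: ρ = .50 with a correction near 0.6 gives 98 over three visits. Each of these values is back-solved; none is in the article.

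**Step 2. The two-group reading, where d = 2f is exact.** The noncentrality is d·√(n/2) = 0.40 × √25 = 2.0 on 98 degrees of freedom, so power is 50.8%. For 95%, n = 164 per arm (328 in total). The result is the same if d = .40 is scaled on the SD of change.

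**Step 3. What f = .20 means for an interaction, with d in raw SDs.** Let D be the between-arm difference in change.

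- Two visits: the interaction deviations in the four cells are ±D/4, so f = D/4. D = 0.40 gives f = 0.10, and f = .20 corresponds to D = 0.80.
- Three visits, arm differences 0, D/2, D: f = D/√24, so f = .20 corresponds to D = 0.20 × 4.90 = 0.98.
- Three visits, arm differences 0, 0, D or 0, D, D: f = D/√18, so f = .20 corresponds to D = 0.20 × 4.24 = 0.85.

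**Step 4. Power for D = 0.40 raw SD with 100 participants.** For two visits the standardised effect on change is 0.40/√(2(1− ρ)):

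| ρ | Effect on change | Power |
|---|---|---|
| .40 | 0.365 | 44% |
| .50 | 0.400 | 51% |
| .76 | 0.577 | 82% |
| .85 | 0.730 | 95% |
| .93 | 1.069 | over 99.9% |

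As a check, the interaction route with f = 0.10 has λ = 100 × 2 × 0.01/(1 − ρ) = 2/(1 − ρ). The squared noncentrality of the change-score t test is 25 × 0.16/(2(1 − ρ)) = 2/(1 − ρ). The two agree.

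At the correlations that return 100 in Step 1, power for D = 0.40 is 44% with two visits (ρ = .40). With three visits (ρ = .25) it is 29% for the linear pattern and 37% for the step patterns.

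**The case against.** The strongest reply is that power here depends on two things the article does not fix: the SD that scales d, and ρ. If d is in raw SDs and the correlation lies in the quoted reliability range of .76–.93, power with 100 participants runs from 82% to over 99.9%, so the claimed 95% may be true. That stands, and it rules out saying flatly that the trial lacks 95% power.

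Other points, and how far each goes:

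- **Cause and effect.** A reader might infer that power is 51% because d = 2f is wrong. The two belong to different readings. Where 51% comes straight from d = .40 with 50 per arm, the conversion is valid. Where the conversion fails, power depends on ρ.
- **Contradiction with the reliability.** A reader might infer that a correlation of .25 or .40 contradicts the protocol's own .76–.93. These values are well below that range, but it is not said to be the correlation over 3 or 6 months. With f held fixed, a low ρ is also the cautious choice.
- **Unseen source.** If f = .20 was itself the interaction effect in the cited study and d only a relabelling, the conversion does not affect N. The documents cannot settle this. The label d = .40 would then mislead, and 100 would still need a back-solved correlation.
- **Condensed article.** Leaving ρ to the full protocol is normal, and its absence alone is not the finding. The finding is that the effect, conversion, power and N that the article does state do not fit together.
- **All 120 analysed.** The intention-to-treat analysis carries last observations forward. At 60 per arm, power is 58% (two-group) or 88% (change, ρ = .76), before any dilution from drop-outs.
- **Small effects.** The background says of other treatments: "These studies have documented small effects in terms of improvements in cognitive tasks". This concerns other products and shorter trials and gives no size, so it does not show that .40 is too large.

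**Conclusion.** The power statement is wrong as written, because its stated inputs do not lead to 95% with 100 participants. On a two-group basis, or with d scaled on the SD of change, power is about 51%, and 95% would need 164 per arm. With d in raw SDs and a two-visit interaction, the d = 2f step doubles the effect actually powered, from 0.40 to 0.80 SD; over three visits f = .20 stands for 0.85–0.98 SD. A 95% figure for a 0.40 SD difference in change needs ρ of about .85 or more.

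These figures assume two-sided α = .05, 50 per arm, equal variances and, for the interaction test, sphericity. The documents do not support the stronger conclusion that the trial has only even odds of detecting its target effect: that is one end of a range running above 99.9% within the quoted reliability. Nor do they establish which scale of d was meant.

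**What to change.** Remove the unqualified 95% claim and the d = 2f step for the interaction. State which contrast the trial will treat as primary, and restate power for it with three things written down: whether d is in raw SDs or SDs of change, the correlation assumed and its basis, and power across a plausible range of correlations.

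If the chosen contrast is a difference in change between two visits, with d in raw SDs, wording such as this would serve:

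> With 100 participants (50 per arm) and a two-sided 5% level, power for a between-arm difference in change of 0.40 raw SD is about 51% if the correlation between the two visits is .50, 82% if it is .76 and 95% if it is .85.

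If d is meant in SDs of change, the figure is about 51% whatever the correlation. If the omnibus three-visit interaction is primary, give its power for a stated pattern of arm differences instead.

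The cost is one rewritten paragraph and a stated power that becomes conditional or less favourable. No additional enrolment is proposed.
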